#### Secondary outcome measures

PASI 75 (proportion (%) of participants achieving a PASI improvement of 75%) (week 12);PASI 50 (proportion (%) of participants achieving a PASI improvement of 50%) (week 12);Relapse rate (return of lesion to 50% of baseline PASI score [40]) (week 24);Change in body surface area (%) (week 12);Change in Dermatology Life Quality Index score (%) (week 12);Skindex 29 score change (%) (week 12);Acceptability and willingness to repeat treatment (week 12);Blood test (full blood, kidney and liver function tests) (weeks 6, 12 and 24);Body mass index change (%) (week 12);Reported adverse events and serious adverse events;Health resource utilization data (medical doctor visits, hospital visits and medication usage).

Acceptability will be measured on an ordinal scale from 0 to 10, where 0 equals very dissatisfied with the treatment and 10 equals very satisfied with the treatment. Willingness to repeat the treatment will be measured on a Likert scale (definitely not, probably not, probably yes, definitely yes or unsure) (week 12). Any adverse events will be recorded by the participant and assessed by blinded assessors at each assessment period.

A full blood count test, as well as liver and kidney function tests, will be completed at weeks -2, 6, 12 and 24 (Table 1). These will measure the impact of the interventions on blood inflammatory markers, as well as monitoring toxicology safety for significant changes in kidney and liver function. Samples of serum will be collected and stored for further investigation of changes to the concentration of key cytokines (weeks -2, 12 and 24). Adverse events will be recorded from participants’ reports and assessors’ observations, then classified as probably related to either Chinese herbal medicine or pharmacotherapy. Any serious adverse event will be reported to RMIT University Human Research Ethics Committee, a data safety and monitoring board and the Therapeutic Goods Administration of Australia. Health resource utilization data will be collected in case report forms; data will include number and reason of hospitalizations, number of medical doctor related visits, reason for visit and use of medication related to psoriasis (frequency and dosage).

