### Potential adverse events

Potential adverse events of calcipotriol are considered minor and may consist of minor skin irritation (including peeling or rash), change in skin colour or skin sensitivity to light [41]. For the YXBCM01, the herbal constituents are commonly used clinically. Minor side effects of YXBCM01 are possible but are not specific to the investigated herbal substances; although uncommon, they may consist of nausea or diarrhoea [42]. If participants develop adverse events or if the results of their blood tests for liver and kidney function become abnormal, participants will be advised to stop all trial-related medication and seek medical advice from their doctors as to their safe continuation in the study.

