### Termination and withdrawal

A data safety and monitoring board of independent experts in pharmacological studies, dermatology and statistics has been formed. The data safety and monitoring board will review and evaluate the study data for safety and study conduct, to make recommendations regarding the continuation, modification or termination of the study. Serious adverse events will be judged according to Therapeutic Goods Administration criteria (2006): ‘Any untoward medical occurrence that at any dose: results in death, is life-threatening, requires inpatient hospitalization or prolongation of existing hospitalization, results in persistent or significant disability/incapacity, is a congenital anomaly or birth defect, or is a medically important event or reaction’ [43]. If judgement is made by the relevant human research ethics committee, Therapeutic Goods Administration, data safety and monitoring board or study investigators that participants are at serious risk as a result of serious adverse event reported in the study, the study will be terminated. In addition, participants are permitted to withdraw at any time throughout the duration of the trial, with or without reason. All withdrawn participants who have received the intervention will be followed-up 8 weeks post withdrawal, to obtain information regarding their condition and any subsequent adverse events.

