### Blinding

Participants, researchers and outcome assessors will be blind to group allocation. Packaging and labelling of study drugs will be conducted by persons independent of the research team. The randomization sequence will be sealed and stored in a locked filing cabinet, separate from participants’ data and only accessible to persons who generated the sequence. Testing of adequate participant blinding will be undertaken at weeks 6, 12 and 24; participants will be asked whether they believe they were given placebo, Chinese herbal medicine or are unsure. Randomization codes will only be broken after data validation and entering processes are complete, or at the request of the human research ethics committee, Therapeutic Goods Administration or the participant’s own physician, if there is identified risk to a participant’s continuation in the study.

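### Acceptability and willingness to repeat treatment are scheduled only at week 12, so participants who leave earlier have no value and the result may overstate acceptability

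*Protocol article*

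**What the plan says.** All references are to the Protocol article.

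- **Timing.** Secondary outcome measures lists "Acceptability and willingness to repeat treatment (week 12"). Blood tests in the same list carry three time points (weeks 6, 12 and 24), so the list names several where several are meant. Table 1 shows no earlier collection of these two items.
- **Scales.** "Acceptability will be measured on an ordinal scale from 0 to 10, where 0 equals very dissatisfied with the treatment" and 10 is the satisfied end. For the second item, "Willingness to repeat the treatment will be measured on a Likert scale (definitely not, probably not, probably yes, definitely yes or unsure) (week 12").
- **Leaving the study.** Under Termination and withdrawal, "participants are permitted to withdraw at any time throughout the duration of the trial, with or without reason". Those who received the intervention are contacted 8 weeks later, "to obtain information regarding their condition and any subsequent adverse events". Neither acceptability nor willingness is named there.
- **Stopping medication.** Under Potential adverse events, participants with adverse events or abnormal liver or kidney tests are advised to stop trial medication and "seek medical advice from their doctors as to their safe continuation in the study". Stopping medication is thus kept apart from leaving the study.
- **Missing data.** Statistical analysis methods prescribes intention-to-treat analysis to limit bias from withdrawals, with last observation carried forward for all missing data.
- **Blinding.** "Testing of adequate participant blinding will be undertaken at weeks 6, 12 and 24".

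**The concern.** The plan relies on carrying the last observation forward to keep withdrawn participants in the analysis. An item asked once, at the end of treatment, has no earlier observation to carry. The one contact the article describes with withdrawn participants is not said to ask it either. Followed as written, the plan yields acceptability and willingness results only for those still in the study at week 12.

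This is a matter of data collection, so a later analysis plan cannot repair it: an answer that was never requested cannot be recovered. The missing answers may well be informative, since dissatisfaction is one plausible reason for leaving. The abstract, Methods/design and Sample size determination all give feasibility of a full trial as a purpose of the pilot, and these two items bear on it. With about 15 participants per arm, two or three unasked leavers can move an arm's mean visibly.

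**Working it through.** **Is there a figure to reproduce?** No. The article gives no dropout rate, acceptability score or standard deviation. The only usable inputs are 30 participants (Sample size determination) and 1:1 allocation (Randomization), hence 30/2 = 15 per arm. The scores and numbers of leavers below are assumptions, shown as a range.

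**Step 1. One arm's mean.** Let k of 15 leave before week 12 without being asked. Let R be the mean of those who answer and L the mean the leavers would have given.

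- Reported mean: R
- Mean over all randomized: [(15 − k)R + kL]/15
- Overstatement: (k/15)(R − L)

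With R from 7 to 8 and L from 2 to 4, the gap R − L runs from 7 − 4 = 3 to 8 − 2 = 6.

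| Leavers k | Smallest gap (3) | Largest gap (6) |
|---|---|---|
| 1 | 3/15 = 0.2 | 6/15 = 0.4 |
| 2 | 6/15 = 0.4 | 12/15 = 0.8 |
| 3 | 9/15 = 0.6 | 18/15 = 1.2 |
| 5 | 15/15 = 1.0 | 30/15 = 2.0 |

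**Step 2. Willingness.** If 9 in an arm are willing and 3 leave unwilling, the week-12 result is 9/12 = 75%, against 9/15 = 60% of all randomized.

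**Step 3. Stopping is not leaving.** Suppose 3 of 15 stop treatment and would score 3, while the other 12 score 7. The mean over all is (12×7 + 3×3)/15 = 93/15 = 6.2.

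- All three still attend week 12: reported 6.2, overstatement 0.
- Half leave the study (expected number 1.5): (84 + 1.5×3)/13.5 = 6.56, overstatement 0.36.
- All three leave: 84/12 = 7.0, overstatement 0.8.

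The gap comes only from those who leave the study.

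**Step 4. Between arms.** The bias in the difference is the Step 1 overstatement in one arm minus that in the other. With three leavers and a gap of 4 in both arms it is 0.8 − 0.8 = 0, although each arm's level is still too high. It is non-zero only if the share leaving, or the gap between responders and leavers, differs by arm.

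**The case against.** Several objections have force.

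- **Those who stop may still answer.** A reader might infer that anyone who stops the granules is never asked. The article does not support that. It separates stopping medication from leaving the study, and a participant who stops but stays can answer at week 12. This stands and narrows the point to those who leave.
- **Inflation is not certain.** A reader might take the outcome to be inflated as a matter of fact. That needs leavers to exist and to be less satisfied, and withdrawal is allowed without a reason. This stands: the result may be overstated.
- **Arms may be affected alike.** A reader might infer that a less acceptable product would look equal. With scores of 8 and 2 and four leavers against none, a true difference of (4/15)×6 = 1.6 points would indeed be reported as zero. That split is an assumption with no basis in the article, and the unequal withdrawal counts would themselves be visible.
- **Blinding.** A reader might infer that blinding success is overstated too. Only those leaving before week 6 lack a guess. They might have guessed rightly, wrongly or been unsure, so the direction is unknown.
- **Other evidence exists.** Adherence checks, measured unused medication and adverse-event records also speak to tolerability. The acceptability item rates the treatment as a whole, calcipotriol included. Rating a course at its end is defensible, and exit ratings describe a shorter exposure. This stands, and it lowers the importance.
- **A condensed article.** An exit questionnaire may exist in the full protocol. That is possible, but the article does state both the time point of the items and the content of the withdrawal contact, and neither provides for these answers.

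**Conclusion.** The point holds as a minor issue on a secondary outcome. Three statements in the article combine to leave early leavers without a value: a single week-12 assessment, a withdrawal contact whose stated content is condition and adverse events, and a carry-forward rule with nothing to carry. The acceptability and willingness results will describe only participants still in the study at week 12.

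Whether and how far this overstates acceptability depends on how many leave and how they would have answered, neither of which the article gives. Under the assumed scores, an arm's mean is too high by 0.4 to 0.8 points with 2 leavers and 0.6 to 1.2 with 3. With no leavers, or leavers as satisfied as those who stay, it is not overstated. Bias between the arms is a further condition and is not shown. Nor do the documents support a direction of bias for the blinding test.

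**What to change.** - In Secondary outcome measures and in Termination and withdrawal, state that both items are asked when a participant withdraws, or at the existing 8-week post-withdrawal contact if missed.
- Keep the week-12 assessment for everyone still in the study, and say that this includes those who have stopped trial medication.
- Report exit answers identifiably alongside the week-12 answers, since they reflect a shorter exposure. Give the number missing and the reasons by arm. For willingness, show withdrawn participants who did not answer as their own category.
- Under Blinding, the treatment-guess question can be put at the same contact to those who leave before week 6, with no claim about the direction of any bias.

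The cost is two or three short questions at withdrawal or at a contact already planned. Some leavers may decline, so the gap would shrink but might not close, and the reported acceptability will probably be less favourable. Trial status says recruitment is under way, so the change helps most if made early: answers from those who have already left may be lost.

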### Potential adverse events

Potential adverse events of calcipotriol are considered minor and may consist of minor skin irritation (including peeling or rash), change in skin colour or skin sensitivity to light [41]. For the YXBCM01, the herbal constituents are commonly used clinically. Minor side effects of YXBCM01 are possible but are not specific to the investigated herbal substances; although uncommon, they may consist of nausea or diarrhoea [42]. If participants develop adverse events or if the results of their blood tests for liver and kidney function become abnormal, participants will be advised to stop all trial-related medication and seek medical advice from their doctors as to their safe continuation in the study.

### Termination and withdrawal

A data safety and monitoring board of independent experts in pharmacological studies, dermatology and statistics has been formed. The data safety and monitoring board will review and evaluate the study data for safety and study conduct, to make recommendations regarding the continuation, modification or termination of the study. Serious adverse events will be judged according to Therapeutic Goods Administration criteria (2006): ‘Any untoward medical occurrence that at any dose: results in death, is life-threatening, requires inpatient hospitalization or prolongation of existing hospitalization, results in persistent or significant disability/incapacity, is a congenital anomaly or birth defect, or is a medically important event or reaction’ [43]. If judgement is made by the relevant human research ethics committee, Therapeutic Goods Administration, data safety and monitoring board or study investigators that participants are at serious risk as a result of serious adverse event reported in the study, the study will be terminated. In addition, participants are permitted to withdraw at any time throughout the duration of the trial, with or without reason. All withdrawn participants who have received the intervention will be followed-up 8 weeks post withdrawal, to obtain information regarding their condition and any subsequent adverse events.

### Sample size determination

A pilot study of 30 participants testing the feasibility of the trial protocol will be conducted prior to a full scale trial. Post-hoc power analysis via effect size estimation on the pilot study data will be used to determine sample size for a full scale trial.

### Randomization, sequence generation and allocation concealment

Participants will be randomly allocated to intervention (YXBCM01 plus calcipotriol) or control group (placebo plus calcipotriol) in equal ratio (1:1). Randomization numbers will be computer generated in blocks and corresponding codes sealed in opaque envelopes. Envelopes will be opened sequentially from each block only after the participant’s details are written on the outside of the envelope. The code inside the envelope will correspond to a package number that will contain 12 weeks supply of either YXBCM01 granules or identically packaged placebo granules.

### Blinding

Participants, researchers and outcome assessors will be blind to group allocation. Packaging and labelling of study drugs will be conducted by persons independent of the research team. The randomization sequence will be sealed and stored in a locked filing cabinet, separate from participants’ data and only accessible to persons who generated the sequence. Testing of adequate participant blinding will be undertaken at weeks 6, 12 and 24; participants will be asked whether they believe they were given placebo, Chinese herbal medicine or are unsure. Randomization codes will only be broken after data validation and entering processes are complete, or at the request of the human research ethics committee, Therapeutic Goods Administration or the participant’s own physician, if there is identified risk to a participant’s continuation in the study.

### Data collection

Data will be collected and recorded in the case report forms from participants via face-to-face and telephone interviews or assessments. Participants will record further daily and weekly data in a home data diary, to be collected by researchers at subsequent assessment or review appointments.

All data will be entered into a pre-designed, password-protected dataset by personnel blinded to group allocation. Data entry will be performed continuously throughout the study using the double-check method, with any correction or changes of written data in participants’ case report forms documented and dated.

### Statistical analysis methods

All data will be analyzed by an independent statistician. The Statistical Package for the Social Sciences software version 21.0 for Windows (SPSS Inc., Armonk, New York, USA) will be used for data analysis. Baseline demographic characteristics on categorical variables, such as sex, will be assessed for balance between the two treatment groups via the chi square test, whilst continuous or interval variables will be assessed for equivalence between the treatment groups by *t* tests. Intention-to-treat analysis will be applied to outcome data to minimize bias due to withdrawals; all missing data will be replaced using the last observation carried forward. Continuous data will be presented as means and standard deviation, or 95% confidence interval. All dichotomous data, such as the percentage of participants achieving PASI 75, will be presented as risk ratio and 95% confidence interval. Other outcomes (for example, severity and quality of life) will be assessed for equivalence in the two groups; *P* < 0.05 obtained from statistical tests on variables involving treatment group comparisons will be considered statistically significant.

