### Trial procedure

The entire trial consists of an initial assessment, a two-week run-in phase (week -2 and -1), a 12-week treatment phase (week 1 to week 12) and a 12-week follow-up phase (week 13 to week 24) (Figure 1).

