### Outcome measures

#### Primary outcome measures

The primary outcome measure will be PASI change (% mean) from baseline to end of treatment (week 12) and end of follow-up phase (week 24) (see Table 1).

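### Last observation carried forward is the only stated rule for missing data: it carries on-treatment PASI to week 24 and can bias the arm comparison in either direction

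*Protocol article*

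**What the plan says.** The Statistical analysis methods section of the protocol article gives one rule and its purpose in a single sentence: "Intention-to-treat analysis will be applied to outcome data to minimize bias due to withdrawals", and then "all missing data will be replaced using the last observation carried forward". It names no other method and no sensitivity analysis.

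Table 1 schedules PASI at week -2, baseline and weeks 6, 12 and 24. Treatment lasts 12 weeks, followed by 12 weeks of follow-up (Trial procedure). The Primary outcome measures section takes percentage PASI change at both week 12 and week 24, although the Abstract names only the end of treatment. Relapse, a secondary outcome, is scored at week 24 as a return to half of the baseline PASI.

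On people who leave, Termination and withdrawal says: "All withdrawn participants who have received the intervention will be followed-up 8 weeks post withdrawal". The purpose given for this contact is "to obtain information regarding their condition and any subsequent adverse events". It does not say that PASI is taken at that contact, or that the scheduled visits continue. Under Potential adverse events, if adverse events or abnormal liver or kidney results occur, "participants will be advised to stop all trial-related medication and seek medical advice" about whether they can safely continue in the study.

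Sample size determination says that the effect size estimated from the pilot will be used to size the full trial.

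**The concern.** The rule assumes that psoriasis stays where it was at the last visit. That is hardest to defend over the follow-up phase, which exists partly to see whether the disease returns once treatment ends. An on-treatment week-12 PASI would stand in for a value measured 12 weeks off treatment.

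The filled-in values are then analysed as if observed. If the arms lose different people, or lose them at different times, the comparison can shift although the treatment has done nothing. That defeats the aim of reducing withdrawal bias, and the shifted effect passes into the sample size of the full trial.

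Read literally, the rule also covers safety data. Blood tests are taken at weeks -2, 6, 12 and 24, so someone who leaves before week 6 would have a pre-treatment liver or kidney result carried forward as an on-study result.

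**Working it through.** The plan gives no dropout rate, relapse rate or PASI trajectory, so there is no figure of its own to reproduce. Only the calendar check in step 1 rests wholly on the document; steps 2 to 4 use assumed rates.

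**1. Reach of the 8-week contact.** Withdrawal at week w is followed to week w + 8.

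| Withdrawal week | Contact ends at week | Reaches week 12? | Reaches week 24? |
|---|---|---|---|
| 1, 2, 3 | 9, 10, 11 | no | no |
| 4 | 12 | yes | no |
| 12 | 20 | yes | no |
| 16 | 24 | yes | yes |

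The contact falls short of week 12 only if w < 4, and short of week 24 if w < 16. The second group includes every withdrawal during treatment.

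**2. Relapse among week-12 responders lost in follow-up.** A responder's week-12 PASI lies below half of baseline, so once carried forward it can never meet the relapse definition. Reported relapse = true relapse × (1 − share lost). Assume a true relapse of 50% in both arms.
- 20% lost in each arm: 0.50 × 0.80 = 40% in both. Relapse is understated, but the arm difference is still zero.
- 10% v 30% lost: 0.50 × 0.90 = 45% and 0.50 × 0.70 = 35%, a false difference of 10 points.

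**3. Week-12 PASI change.** Assume 60% true improvement in both arms, a week-6 improvement 70% as large (0.70 × 60 = 42%), and 10% (active) v 30% (control) leaving between weeks 6 and 12.
- Carried forward: active 0.90 × 60 + 0.10 × 42 = 58.2; control 0.70 × 60 + 0.30 × 42 = 54.6; difference +3.6 points.
- If leavers would have done as well as completers, the true difference is 0 and the bias is +3.6.
- If leavers returned to baseline, the true difference is 0.90 × 60 − 0.70 × 60 = 12.0 and the bias is 3.6 − 12.0 = −8.4.
- Swapping the dropout rates reverses both signs.
- If everyone leaves before week 6, so that baseline is carried, the reported difference is 54 − 42 = +12 points. The bias is +12 if leavers would have done as well as completers and 0 if they stayed at baseline.
- Equal loss is not always safe. With true improvements of 60% v 45% and 20% leaving each arm after week 6, the rule gives 56.4 − 42.3 = 14.1. The true difference is 15 (bias −0.9) if leavers match completers, or 48 − 36 = 12 (bias +2.1) if they return to baseline.

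**4. Relapse can also be overstated.** Assume 15 per arm, 3 lost, and 5 of 12 completers relapsing (41.7%). If the 3 were week-12 responders, the rule gives 5/15 = 33.3%. If their last value is baseline and relapse is not restricted to responders, they sit at 100% of baseline and could be counted as relapsed: 8/15 = 53.3%. With one pattern in each arm, identical completer data give a risk ratio of 5/8 = 0.625 or 8/5 = 1.6.

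**The case against.** The rule is pre-specified and applied alike to both arms, the values carried are real earlier measurements, and sensitivity analyses may sit in an analysis plan that is not shown. This is a 30-participant pilot whose main aim is feasibility. In the relapse example the false 10 points amount to 1.5 participants if all 15 in each arm were responders, which is generous. The standard error of that difference is √(0.45 × 0.55/15 + 0.35 × 0.65/15), about 18 points. All of this stands and bears on severity. It does not rescue the rule: the plan fixes it for all missing data, and equal application does not give equal bias when loss or trajectories differ.

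A reader might infer more than the document supports, on three points.
- That the 8-week limit is why week-12 PASI will be missing. It falls short of week 12 only for those who leave before week 4, and anyone who leaves after week 12 has a week-12 PASI. The section also does not say that scheduled visits stop; it is silent on that and on PASI.
- That loss will certainly be related to treatment. The adverse-event text concerns stopping medication and contemplates continuing in the study, so it makes such loss possible, not certain.
- That missing week-24 status should simply be counted as failure. With 10% v 30% lost, that turns 45% v 35% into 0.45 + 0.10 = 55% v 0.35 + 0.30 = 65%, the same false gap with the sign reversed.

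**Conclusion.** The concern holds, chiefly for week 24. As the sole stated rule, last observation carried forward sets early leavers to 0% change at both primary time points and prevents lost week-12 responders from being counted as relapsed. Within an arm it understates relapse among those responders. Between arms the sign cannot be known in advance. Under the assumed rates, the bias in week-12 PASI change runs from −8.4 to +3.6 points when week 6 is carried, with the signs reversed if dropout is reversed, and reported relapse is 45% v 35% where the truth is 50% in both. With equal loss and equal arms the bias in the comparison is zero. The sizes rest on assumed dropout, relapse and trajectories.

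The 8-week contact does not fill the week-24 gap for anyone who withdraws during treatment. Because the pilot effect sizes the full trial, the plan should be changed; the small size and feasibility purpose keep this below a critical fault.

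**What to change.** 1. **Termination and withdrawal.** State that participants who stop study medication or withdraw from treatment, unless they withdraw consent to data collection, are asked to attend the scheduled week 6, 12 and 24 assessments. Keep the 8-week contact. This concerns data collection only and alters no treatment rule.
2. **Statistical analysis methods, continuous outcomes.** For PASI, body surface area, Dermatology Life Quality Index and Skindex 29, replace the carry-forward rule with a likelihood-based repeated-measures model with arm-by-visit terms, or with multiple imputation. Enter baseline as an outcome with a common mean across arms. With baseline only as a covariate, participants with no later PASI would drop out of the analysis. The model is then for the score, with percentage change derived from it; multiple imputation allows percentage change to be computed per participant.
3. **Binary outcomes.** Derive PASI 50, PASI 75 and relapse from multiply imputed PASI, or score missing PASI 50/75 as non-response. Assess relapse among week-12 responders, and show the range with missing status counted as relapsed and as not relapsed in each arm. In the example above the ranges are 45% to 55% and 35% to 65%, and both contain the true 50%.
4. **Safety and sensitivity.** Do not impute adverse events or laboratory values. Keep last observation carried forward only as a sensitivity analysis, alongside one that departs from missing at random.

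The cost is a little more analysis work, some visits by participants who have stopped treatment, and somewhat wider confidence intervals. The article reports the trial as recruiting, and codes are broken only after data validation and entry unless a participant is at risk, so the change can be made blind.

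### The risk ratio, the one between-group measure named for dichotomous data, cannot be relied on for uncommon outcomes at about 15 per arm; counts and a risk difference should stand beside it

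*Protocol article*

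**What the plan says.** The section on statistical analysis methods sets one rule for binary outcomes: "All dichotomous data, such as the percentage of participants achieving PASI 75, will be presented as risk ratio and 95% confidence interval". No second comparative measure appears there for these data.

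The outcomes that the rule covers are in the list of secondary outcome measures:

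- "PASI 75 (proportion (%) of participants achieving a PASI improvement of 75%) (week 12"), and PASI 50 in the same form;
- "Relapse rate (return of lesion to 50% of baseline PASI score [40]) (week 24");
- "Reported adverse events and serious adverse events", where these are analysed as yes or no per participant.

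On size, the sample size section says "A pilot study of 30 participants testing the feasibility of the trial protocol will be conducted prior to a full scale trial", and the randomization section allocates "in equal ratio (1:1"). Fifteen per arm follows from these two statements; the article does not state it. Missing data are carried forward under intention to treat, so efficacy denominators should stay near 15.

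No expected rate is given for any dichotomous outcome. The nearest statement is in the section on potential adverse events, on side effects of YXBCM01: "although uncommon, they may consist of nausea or diarrhoea".

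**The concern.** A risk ratio divides by the control proportion, and its usual interval is built on the log scale. Both steps need at least one event in each arm. In a trial of this size an uncommon outcome may well have no events in an arm, and then the named measure fails in one of three ways:

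- no control events: no finite estimate;
- no events on YXBCM01: an estimate of 0 without a standard interval;
- no events in either arm: 0/0.

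An analyst who adds a constant to the cells gets a number, but the constant largely decides it.

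Safety of the combination is one of the two stated objectives, and serious or individual adverse events are the outcomes most likely to be sparse. On the efficacy side, a clear excess of PASI 75 responders over an empty control arm would have no finite ratio, although the data carry usable information.

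**Working it through.** **Inputs.** N = 30 (sample size section) and 1:1 allocation (randomization section), so n = 15 per arm. The article states no power or event rate, so there is no planned figure to reproduce. The true rate p is an assumption, shown as a range.

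**Step 1: chance of an empty arm.** For one arm, P(no events) = (1 − p)^15. For at least one empty arm when both share the rate, P = 1 − [1 − (1 − p)^15]².

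| Assumed rate p | One given arm empty | At least one arm empty |
|---|---|---|
| 2% | 74% | 93% |
| 5% | 46% | 71% |
| 10% | 21% | 37% |
| 15% | 9% | 17% |
| 20% | 3.5% | 7% |
| 30% | 0.5% | 0.9% |

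Solving (1 − p)^15 = 0.10 gives p = 1 − 0.10^(1/15) = 14%. An arm therefore has a 10% or greater chance of being empty only when its true rate is about 14% or lower.

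**Step 2: an illustrative result, PASI 75 in 5/15 v 0/15 (assumed data).** The uncorrected ratio is (5/15)/(0/15), which has no finite value. With a constant k added to each cell, the ratio is (5 + k)/k:

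| k | Risk ratio | 95% CI |
|---|---|---|
| 0.25 | 21 | 0.40 to 1,091 |
| 0.5 | 11 | 0.66 to 183 |
| 1 | 6 | 0.81 to 45 |

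For k = 0.5, the standard error of the log ratio is √(1/5.5 − 1/16 + 1/0.5 − 1/16) = 1.434, and 11 × exp(±1.96 × 1.434) gives 0.66 to 183.

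**Step 3: the same data as a risk difference.** The Wilson limits are 0.152 to 0.583 for 5/15 and 0 to 0.204 for 0/15. The Newcombe limits are:

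- lower: 0.333 − √[(0.333 − 0.152)² + (0.204 − 0)²] = 0.060;
- upper: 0.333 + √[(0.583 − 0.333)² + (0 − 0)²] = 0.583.

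The difference is 33 percentage points (6 to 58), without any correction. Fisher's exact two-sided P is 0.042. The corrected risk-ratio intervals all include 1, while the risk-difference interval excludes 0, so the choice of measure changes how this result reads.

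**Step 4: sparse safety data.** One serious adverse event v none (1/15 v 0/15) again gives no finite ratio; the risk difference is 6.7 points (−14 to 30). For 0/15 v 0/15 the ratio is 0/0; the difference is 0 (−20 to 20), which tells the reader how little the trial can exclude.

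**The case against.** Four points on the other side deserve weight.

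- **The text does not exclude other summaries.** A reader might infer that the risk ratio is the sole permitted presentation. The article does not say so: the same sentence speaks of a percentage of participants, and PASI 75 and PASI 50 are defined as proportions. Per-arm percentages would probably be visible. This stands. What remains is that no other comparison between arms, with an interval, is named.

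- **Zero-cell rules belong in an analysis plan.** The interval method and any continuity correction are details that an article may leave to a document not shown here, so their absence is no fault. A score interval for the risk ratio also needs no correction: for 5/15 v 0/15 it runs from 1.51 to infinity. That too stands, but such an interval gives only a lower bound and no finite estimate. The point concerns the measure that the article chose.

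- **Rarity is not established.** A reader might infer that any dichotomous outcome here could easily be empty in an arm. The documents do not support that. Both arms receive calcipotriol, which the article describes as effective and which may irritate the skin, so neither response nor adverse events of any kind need be rare in controls. The Discussion's remark on rarity concerns complete clearance, which is not a listed outcome, and not PASI 75. At 30% or more the problem all but disappears.

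- **No general bias towards 1.** A reader might also infer that reporting only the ratios that can be computed pulls the result towards 1. That happens at 20% on YXBCM01 v 5% on control, where the mean ratio given at least one control event is 2.49 against a true 4. At 5% in both arms the mean is 0.62 against a true 1, which is away from 1. The direction depends on the rates, so no such claim is made.

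**Conclusion.** The point holds as a minor one. The article commits all dichotomous data to a measure that has no finite estimate, or no standard interval, whenever an arm is empty. At about 15 per arm that happens with probability 46%, 21% and 9% per arm at true rates of 5%, 10% and 15%, and under 1% at 30% or more. These rates are assumptions, because the documents supply none.

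The exposed outcomes are serious or individual adverse events, and PASI 75 if few controls respond. For PASI 50, relapse or any other outcome that proves common, the risk ratio will usually be estimable. The primary outcome is the continuous change in PASI and is unaffected. Everything affected is a secondary or safety outcome in a feasibility pilot, so this is a cheap improvement and no threat to the trial.

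**What to change.** Amend the sentence on dichotomous data in the statistical analysis methods along these lines: dichotomous outcomes will be presented as n/N (%) per arm and as a risk difference with a Newcombe (hybrid score) 95% confidence interval, with Fisher's exact test where a P value is given; the risk ratio with 95% confidence interval will be given in addition where it can be estimated.

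Because the risk difference is always reported, no comparison drops out when an arm is empty. The risk ratio should be read as supplementary, since it would still appear only for data sets that allow it.

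No data, visits or participants are added. The costs are one more measure per outcome and perhaps a short formula or macro in the named software. Fisher's test and the Newcombe interval can also disagree near the boundary: for 4/15 v 0/15 the interval is 0.9 to 52.0 points while P is 0.10. The sentence could say that the interval is the main summary.
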